### Interventions

Participants allocated to the offer of homeopathic treatment or the offer of supportive listening are offered up to five one hour appointments at Barnsley Hospital over a six month period. Due to the pragmatic nature of this trial it will be for the participants to decide as to whether or not they attend all five sessions, however they will be encouraged to attend appointments as would be the case in usual practice. All participants remain in the care of their GP and continue to receive their usual NHS treatments. Homeopathic treatment involves a homeopathic consultation followed by the prescription of a homeopathic medicine and is provided by professional homeopaths registered with the Society of Homeopaths with at least five years experience. The homeopaths providing treatment in this study do not have a particular specialism in IBS, however they have taken part in a previous trial assessing the effectiveness of homeopathic treatment for fibromyalgia
[30]. The homeopaths can choose from any of the homeopathic medicines in the homeopathic pharmacopeia.

Supportive listening is based on the theories and counselling techniques of Carl Rogers
[31] and involves active listening skills such as empathising, reflecting, summarising and paraphrasing. In the sessions patients are able to talk about their physical symptoms as well as any emotional issues and possible ways of coping with these better. It provides patients with the opportunity to express themselves and feel heard in a non-judgemental environment. The sessions are delivered by trained psychotherapists registered with either the British Association for Counselling & Psychotherapy or the United Kingdom Register of Counsellors and Psychotherapists. For intervention fidelity, and to ensure that the practitioners delivering the supportive listening are delivering supportive listening rather than Cognitive Behavioural Therapy or any other counselling intervention, a random selection of sessions is taped and assessed by an independent assessor, who will describe the approaches used.

The patients’ perceptions of the effects of interventions and their acceptability to patients will be assessed in a nested qualitative study exploring patient and practitioner experiences of delivering and receiving treatment within the trial. This qualitative study will take the form of hour-long semi-structured interviews aimed at eliciting information about what, it anything patients perceive to have led to any improvement in their IBS or general health. The aim being to explore patients perceptions of the treatment they received, what, if anything they believe led to any effectiveness the treatment and their views on the acceptability of the treatment. It is the intention to publish full details of the qualitative study at a later date.

### Outcome measures

The primary outcome measure is the IBS Symptom Severity Scoring (IBS-SSS)
[32]. Secondary outcome measures are the Hospital Anxiety and Depression scale (HADs)
[33] and EQ-5D
[34]. The EQ-5D was chosen as the quality of life measure rather than a disease specific measure such as the IBS quality of life measure (IBS-QOL)
[35] because the EQ-5D was required for the cost effectiveness component of this study. Therefore to reduce the burden of filling out multiple questionnaires on patients it was decided to utilise solely the EQ-5D rather than an additional disease specific health related quality of life measure.

Cost effectiveness is calculated using the EQ-5D, a measure of health related quality of life along with data collected on medication and health services usage and absences from work.

The credibility of the treatments to the patients is assessed using a validated measure originally designed by Borkovec
[36] and modified by Drossman
[37] for IBS. A single measurement at 26 weeks is made using the CARE empathy measure for participants in either the homeopathic treatment or supportive listening arms
[38]. This is a measure of the practitioner’s empathy as perceived by the patients.

Outcomes are sought by postal questionnaire at baseline, 26 weeks and 52 weeks. The primary endpoint of this study is 26 weeks, whilst the 52 week questionnaire will provide data on the longer term effectiveness of the interventions.

### Sample size

The RCT sample size calculation has been based on the primary outcome, which is the change in IBS-SSS between baseline and 26 weeks. The IBS-SSS is based on a series of visual analogue scales (VAS) and has been validated for use in assessing IBS severity. It is scored between 0 and 500 and a higher score indicates more severe IBS. A change of 50 points is considered to be a clinically relevant change
[32]. It has been suggested that VAS scales are of greater value when used to determine change within individuals rather than being used to compare scores at a set time frame across a group of individuals
[39]. Therefore change in IBS-SSS is used rather than an endpoint score. This study has been powered to detect a difference between homeopathic treatment and usual care. Powering to detect a difference between homeopathic treatment and supportive listening was considered but found to be beyond the resources of this study. However the study will still be able to provide information on the feasibility of supportive listening as an attention control for homeopathic treatment.

A 4:1:1 ratio of usual care: homeopathic treatment: supportive listening was chosen for this trial because of cost limitations. The cost of providing homeopathic treatment or supportive listening was higher than costs associated with the usual care arm of the trial. Using unequal group size provides a means of reducing the cost of a trial whilst maintaining power
[40]. A power calculation was carried out using sample size determination software called PS Power
[41]. Assuming use of an independent *t* test to compare groups, power 80%, significance level 5%, clinically relevant change of 50 on the IBS-SSS
[32] and based on previous RCTs
[42-44] standard deviation of 85, ratio of usual care to homeopathic treatment of 4:1, 29 participants are required for the homeopathic treatment and supportive listening arms and 116 for the usual care arm for this comparison. In a previous IBS study
[45] it was found that there was a 13% loss to follow up and taking this into account increases the estimated sample size to 33 for the homeopathic treatment and supportive listening arms and 132 for the usual care arm. Therefore in total 198 people will be required for this study, 33 people for each of the homeopathic treatment and supportive listening arms and 132 people for the usual care arm.

### Data analysis

Descriptive statistics and a CONSORT type flow diagram
[46] are used to describe the flow of all participants through the trial. The following baseline patient characteristics are reported for all participants meeting the RCT criteria: age, IBS-SSS, HAD score, number of prescribed/self prescribed medications, medication total and EQ-5D score. Baseline data on those who accepted the offer of treatment and those who refused are compared to assess whether there are any differences between those who accepted and those who declined treatment.

Data are analysed on an intention to treat basis using a 2-sided 5% significance level. All participants are included in the group they were randomised to regardless of whether they received their allocated treatment. The primary outcome is the mean change in IBS-SSS between baseline and 26 weeks assessed using analysis of covariance adjusting for baseline scores. The percentage of those achieving a clinically relevant change of 50 points on the IBS-SSS will be reported for each of the three groups. The mean change in HADS between baseline and 26 weeks will also be assessed using analysis of covariance adjusting for baseline scores. All data are tested for normality and where normality is not met the equivalent nonparametric tests will be used.

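### The normality rule lets the observed data replace the primary ANCOVA with a rank test, which no longer addresses the mean difference on which the trial was sized

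*Protocol article*

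**What the plan says.** All of this is in the protocol article.

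- Data analysis, primary analysis: "The primary outcome is the mean change in IBS-SSS between baseline and 26 weeks assessed using analysis of covariance adjusting for baseline scores". HADS change is to be analysed in the same way.
- Data analysis, error rate: "Data are analysed on an intention to treat basis using a 2-sided 5% significance level".
- Data analysis, closing sentence: "All data are tested for normality and where normality is not met the equivalent nonparametric tests will be used". It makes no exception for the primary outcome, does not name the substitute test, and does not say that ANCOVA remains primary.
- Sample size: an independent t test with "power 80%, significance level 5%, clinically relevant change of 50 on the IBS-SSS" and "standard deviation of 85, ratio of usual care to homeopathic treatment of 4:1", giving "29 participants are required for the homeopathic treatment and supportive listening arms and 116 for the usual care arm for this comparison".

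**The concern.** The first sentence fixes a method and an estimand: the baseline-adjusted difference in mean change, in IBS-SSS points. The closing sentence makes both conditional on how the outcome data turn out.

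- **The estimand changes.** A rank test addresses a shift in ranks. Its result cannot be read against 50 points, the difference on which the sample size rests.
- **The check is aimed at the wrong quantity.** ANCOVA assumes normal residuals, not normal data. At this sample size, inference on a mean is robust to moderate departures even in the residuals.
- **ANCOVA has no single rank equivalent.** Mann-Whitney or Kruskal-Wallis on change would also drop the baseline covariate. A rank ANCOVA would keep it, but would still lose the mean difference.

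At stake is whether the trial's main result is an effect in points, adjusted for baseline, or something else that is known only after the outcomes are in.

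**Working it through.** **1. The plan's own figure.** Inputs from Sample size: difference 50, SD 85, ratio 4:1, two-sided 5%, power 80%.

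n (smaller arm) = (1 + 1/4) × (1.960 + 0.842)² × (85/50)² = 1.25 × 7.849 × 2.89 = 28.35, rounded up to 29; 4 × 29 = 116. Exact t-test power at 29 v 116 is 80.4%. The stated 29 and 116 are reproduced. The inflated 33 and 132 follow from 29 × 1.13 = 32.8 and 116 × 1.13 = 131.1, rounded up. Every step rests on a difference in means.

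**2. What ANCOVA gives at 29 v 116.** Assume that 85 is the SD of change, that variances are equal at the two times, and that baseline and 26 weeks correlate at r. The article does not give r, so 0.3, 0.5 and 0.7 are used.

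Residual SD = 85 × √((1 + r)/2) = 68.5, 73.6, 78.4.

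Power = Φ(50 / (residual SD × √(1/29 + 1/116)) − 1.96) = 94.0%, 90.5%, 86.7%.

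Unadjusted Mann-Whitney on change under normality has relative efficiency 0.955: Φ(50/(85 × 0.2076) × √0.955 − 1.96) = 79.1% at every r.

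**3. Simulation of the rule.** 29 v 116, SD of change 85, 3000 trials per setting. Follow-up errors are normal, skewed (skewness 1) or t with 5 df. Assumed rule: Shapiro-Wilk at 5%, applied either to change within each arm or to the ANCOVA residuals; if it rejects, Mann-Whitney on change replaces ANCOVA.

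How often the rule fires:
- normal errors: 9–10% (arms) or about 5% (residuals)
- skewness 1: 56–87% or about 99%
- t5: 39–59% or 67–69%

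Type I error over all settings: ANCOVA always 4.7–5.7%; the rule 4.7–5.4%. Monte Carlo standard error is √(0.05 × 0.95/3000) = 0.4 percentage points.

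Power (%) at a 50-point difference:

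| Errors | r | ANCOVA always | Mann-Whitney always | Rule, change by arm | Rule, residuals |
|---|---|---|---|---|---|
| Normal | 0.3 | 93.1 | 78.4 | 91.4 | 92.5 |
| Normal | 0.5 | 88.6 | 76.8 | 87.7 | 88.1 |
| Normal | 0.7 | 86.5 | 77.5 | 85.7 | 86.1 |
| Skewness 1 | 0.3 | 92.6 | 78.4 | 84.4 | 78.5 |
| Skewness 1 | 0.5 | 89.9 | 80.6 | 83.4 | 80.6 |
| Skewness 1 | 0.7 | 86.0 | 81.5 | 82.5 | 81.6 |
| t5 | 0.3 | 94.0 | 82.6 | 90.4 | 86.7 |
| t5 | 0.5 | 89.6 | 82.8 | 87.1 | 85.9 |
| t5 | 0.7 | 86.9 | 86.0 | 88.0 | 87.5 |

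Loss against ANCOVA at skewness 1 (r = 0.3, 0.5, 0.7): 8.2, 6.5 and 3.5 points if change is tested by arm; 14.1, 9.3 and 4.4 if residuals are tested. With t5 errors and r = 0.7 the rule is 0.6–1.1 points ahead, so there is no loss.

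**4. If the substitute were rank ANCOVA.** In a further simulation at skewness 1, rank ANCOVA had 93, 91 and 83% power against 93, 91 and 87% for ANCOVA (r = 0.3, 0.5, 0.7). The power loss largely disappears. The change of estimand does not.

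**The case against.** The best defence is that little measurable harm follows, and most of it stands.

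- **Baseline adjustment.** A reader might infer that the rule discards the baseline covariate. The article does not say so, because the substitute is unnamed and rank ANCOVA would keep it. Losing the covariate is the natural reading, not a stated one.
- **Power.** A reader might infer that power is lost whenever the rule fires, or that the trial becomes underpowered. Neither is supported. The t5 rows show small or no losses at high correlation, and with heavier tails (t3, r = 0.7) a separate run had the rule ahead, 93% v 87%. The planned 80% assumed an unadjusted t test, and the lowest simulated power under the rule is 78.5%. The loss is relative to the ANCOVA that the plan itself chose.
- **False positives.** A reader might infer that a data-driven choice inflates type I error. The simulation shows no material inflation. The Randomisation and blinding section also says that analysis is blind to allocation, which limits deliberate steering.
- **Missing detail.** That the normality test, its level and the variable tested are not given is something a condensed article may leave to a fuller document. It is not counted here.
- **Responder percentage.** The share of each group reaching a 50-point change is reported in any case. That keeps some contact with the scale, but a within-person responder proportion does not replace a between-group difference in means.

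None of this answers the central point. The switch is a stated rule, it covers the primary outcome, and after it fires the adjusted mean difference is no longer what is tested.

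**Conclusion.** Wrong as written, of moderate severity. The article states a rule under which the observed data decide whether the primary test addresses the adjusted mean difference. That conclusion comes from the text and needs no simulation.

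The simulation adds two things. ANCOVA holds its error rate at these sizes under skewness 1 and t5 tails, so the switch buys no needed protection. If the substitute is Mann-Whitney on change, the rule costs about 4–14 percentage points of power relative to ANCOVA at skewness 1, and little or nothing with heavy tails and high correlation. These sizes rest on the assumed correlation of 0.3–0.7, the error shapes, Shapiro-Wilk at 5%, and 85 being the SD of change.

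**What to change.** For IBS-SSS and HADS, delete the switching sentence and replace it with wording such as: *Baseline-adjusted ANCOVA is the analysis of change whatever the distribution of the data. Residuals will be inspected graphically. A bootstrap or robust-standard-error 95% confidence interval for the same adjusted mean difference will be given as a sensitivity analysis. Any rank-based analysis is a sensitivity analysis only.*

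This should be settled before outcomes are examined. The cost is one sentence of wording and a little extra analysis; the design, sample size and data collection are unchanged.

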## Discussion

This research received ethics approval from the Leeds East Research Ethics Committee (10H/1306/73).Results are expected in 2013.
